### **6.7 Study discontinuation criteria**

Based on the study's characteristics and considering previous experiences, there is no anticipation of needing to interrupt the study due to safety concerns or lack of efficacy. Consequently, there will be no interim analysis conducted for these purposes, nor is the presence of a dedicated safety committee required. If any serious adverse events do arise, the trial research team will be responsible for their evaluation.

### **6.8 End of trial**

The trial will conclude on the date of the last scheduled visit, with an anticipated total follow-up period of 24 months. Primary results analysis is planned at the 12-month mark. The subsequent 12 to 24 months will serve as a pragmatic extension with passive follow-up, excluding telephone reminders by the collaborating researchers. A final visit for patients remaining in the study will capture a reduced set of outcome variables (secondary endpoints).

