#### **6.1.2 Secondary outcome measures**

1. Difference in mean systolic blood pressure, in mmHg at 6 and 24 months of follow-up between intervention and control groups determined at physicians' practice with a validated automatic electronic sphygmomanometer.
2. Difference in mean diastolic blood pressure, in mmHg at 6, 12 and 24 months of follow-up between intervention and control groups determined at physicians' practice with a validated automatic electronic sphygmomanometer.
3. Percentage of patients with SBP <140 mmHg and DBP <90 mmHg at 6, 12 and 24 months of follow-up.

4. Quality of life (as measured by EuroQoL-5D) at 6, 12 and 24 months of follow-up.
5. Adherence measured by proportion of days covered (PDC) at 6 and 12 months of follow-up.
6. Persistence, defined as period of continuous use of the corresponding drug from the beginning of the follow-up until its discontinuation at 6 and 12 months of follow-up.
7. Therapeutic inertia (TI), defined as the number of patients whose pharmacological treatment had not been modified, divided by the number of patients not reaching the target values (SBP and/or DBP measurements taken at 6 and 12 months of follow-up), according to the recommendations of the European Society of Hypertension and European Society of Cardiology (19).

Other outcome measures:

1. Changes in lifestyle (smoking, exercise, body weight) at 6, 12, and 24 months compared to these characteristics at baseline.
2. Clinical events: We will assess if any of the following adverse events are present during the follow-up: angina, myocardial infarction, stroke, hypotensive crisis and death.
3. Use of health services for hypertension at 6, 12 and 24 months.
4. Incremental cost per quality-adjusted life year gained in the intervention group compared to the control group.
5. Views and experiences of patients and health professionals on the self-management (SMBP plus self-titration) of hypertension.

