### **7.3 Expected criteria for withdrawal of study subjects**

#### **7.3.1 Voluntarily drop out of the study**

#### **7.3.2 For non-compliance or violation of the rules contained in the protocol**

Participating patients will have the right to withdraw from the study at any time. Additionally, the investigator may discontinue a patient from the study if she deems it necessary for any reason, including:

- Ineligibility (retrospective if not detected at enrollment)
- an adverse event leading to inability to fulfill with trial procedures
- disease progression leading to inability to fulfill with trial procedures
- withdrawal of consent
- lost to follow-up

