#### **7.3.3 Women who become pregnant during the follow-up period of the study**

Since the study includes individuals over the age of 40, there is a possibility of pregnancy during the follow-up period. However, due to the naturalistic conditions of the study, it is not deemed necessary to mandate contraceptive measures for women of childbearing age. Doing so could introduce additional risks. It's important to note that the ADAMPA protocol does not involve drug administration, and any risks associated with drug treatments are unrelated to the study. These risks would arise from medications prescribed by a participant's doctor, regardless of their involvement in the study. Nonetheless, pregnancy can complicate the management of hypertension and vice versa, necessitating specific and distinct medical monitoring beyond what's outlined in the intervention protocol. Consequently, if a participant becomes pregnant during the follow-up period, they will be excluded from the assigned protocol. Instead, their care will be overseen by their doctor(s), while still maintaining their endpoint follow-up and inclusion in the intention-to-treat analysis.

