### **7.4 Procedures to Follow for Patients Leaving the Study**

We will employ an intention-to-treat approach for outcome analysis. This means that all patients will be included in the analysis based on their randomized arm, even if they discontinue the trial, do not fully adhere to the intervention, or deviate from the protocol. All participants, including those who face these challenges, will be invited to attend follow-up visits at 6, 12, and 24 months. In cases of complete loss of a patient, they cannot be included in the primary analysis since the main outcome measure will not be available. If a participant abandons the study, we will document the reason in the Case Data Report (CDR) whenever possible.

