### **8.4 Schedule of visits and evaluations**

The baseline visit will be made to the patients after selection by their responsible physician. Additionally, patients will be visited at 6 and 12 months. A last visit will be made at 24 months to the patients who continue in the study. The data that will be collected at each time point is shown in **Table 2** of section 6.6.

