#### 8.5.3 Follow-up visits

- 6-Month Visit:
  - o Researchers will record data related to the variables of the follow-up visit (as outlined in **Table 2** of section 6.6). Data sources will include information provided by the patient, the Patient's Notebook, and the patient's electronic medical record.
  - o All patients, regardless of their group, will receive a 6-month follow-up appointment and will be informed that they will receive a reminder call beforehand. They should also bring their completed Patient's Notebook.
- 12-Month Visit:
  - o Researchers will collect data related to the variables of the follow-up visit (as detailed in **Table 2** of section 6.6), using information from the patient, the Patient's Notebook, and the electronic medical record.
  - o Patients, irrespective of their group, will be informed that they will continue with their group-specific trial instructions (self-monitoring/self-adjustment or usual care). Simultaneously, they will maintain their regular medical and nursing appointments. They will also be informed that they will receive a phone call for a final visit within a year and should bring their completed Patient's Notebook.
- 24-Month Visit:
  - o During this visit, a reduced set of outcome variables will be collected, including blood pressure, quality of life, and use of healthcare services (as outlined in **Table 2** of section 6.6).
  - o The purpose of this visit is to conduct secondary analyses after a period of passive follow-up. This aims to evaluate adherence to the intervention under conditions even closer to usual clinical practice. Additionally, results at 24 months will be obtained during this visit.

- During the period from months 12 to 24, MICs will not provide reminders, and nurses will carry out complementary assistance work alongside MEFIs for follow-up, adjustment plan renewals, etc.

If the patient does not attend the follow-up visits, the patient will be located by telephone to give a new date of visit or, in the event that he is not located or leaves the study, the date and the reason for it will be recorded. Any data collected from patients that does not appear in their clinical history will be included in it.

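### Sections 6.8 and 8.4 limit the 24-month visit to patients still in the study, while 7.4 invites all participants, so 24-month secondary comparisons could omit a group selected after randomisation

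*Protocol*

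**What the plan says.** Section 6.8 describes the end of follow-up: "A final visit for patients remaining in the study will capture a reduced set of outcome variables". Section 8.4, the visit schedule, says: "A last visit will be made at 24 months to the patients who continue in the study". In 8.4 this limit applies to month 24 only; the 6- and 12-month visits carry no such condition.

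Section 7.4, which deals specifically with patients who leave, takes the opposite line. Its intention-to-treat statement covers patients "even if they discontinue the trial, do not fully adhere to the intervention, or deviate from the protocol", and it continues: "All participants, including those who face these challenges, will be invited to attend follow-up visits at 6, 12, and 24 months".

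Section 8.5.3 does not restrict its 24-month entry to continuers, and it has non-attenders phoned for a new date. But "in the event that he is not located or leaves the study, the date and the reason for it will be recorded", with no mention of a further measurement.

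Two other places bear on the point. Under 7.3.2, "the investigator may discontinue a patient from the study if she deems it necessary for any reason". Under 7.3.3, women who become pregnant come off the assigned protocol "while still maintaining their endpoint follow-up and inclusion in the intention-to-treat analysis".

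The month-24 results are named secondary outcomes. The first in 6.1.2 is "Difference in mean systolic blood pressure, in mmHg at 6 and 24 months of follow-up between intervention and control groups"; DBP, the percentage with controlled BP and EQ-5D at 24 months are also listed.

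**The concern.** A patient who has discontinued the trial is invited at month 24 under 7.4 and is outside the visit under 6.8 and 8.4. The protocol does not say which rule governs.

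Being still in the study is settled after randomisation. It depends partly on the decision of a family physician who knows the allocation (6.3.2), and the grounds listed in 7.3.2 include adverse events and disease progression that leave a patient unable to carry out trial procedures. Those procedures differ by arm: the intervention arm has to measure and self-adjust, while controls receive information and usual care. Discontinuation may therefore differ between arms and may be related to blood pressure.

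The month-24 visit is where the protocol asks whether the intervention works under conditions closer to routine practice (8.5.3, 8.5.4). If patients who discontinued but could have attended are not measured, that comparison is no longer between the groups as randomised.

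**Working it through.** 1. The plan's own figures. The protocol gives no retention or sample-size figure for month 24. Its only related figure is for 12-month SBP in 11.1. With a 5 mmHg difference, SD 15, two-sided alpha 0.05 and 90% power, the normal formula gives 2 × (1.960 + 1.282)² × 15²/5² = 189.1, so 190 per arm and 380 in total. The t-based solution is 190.1, so 191 per arm and 382 in total, which matches. Then 382 × 1.2 = 458.4, stated as 458. Nothing in this point disputes these figures.

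2. The sections side by side, for a patient who has discontinued but is alive, consenting and able to attend:

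| Section | Seen at month 24? |
|---|---|
| 6.8 | No: visit is for those remaining |
| 8.4 | No: visit is for those continuing; no such limit at 6 and 12 months |
| 7.4 | Yes: invited |
| 8.5.3 | Unclear: visit entry unrestricted, but only date and reason recorded for a leaver |
| 7.3.3 | Yes, in the one case it covers (pregnancy) |

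3. From visit to analysis. Section 11.2 sets an intention-to-treat basis on complete cases and gives similar methods for secondary outcomes. A patient with no month-24 reading is then absent from the main month-24 comparison.

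4. Formula for the bias. In each arm let d be the share of patients not measured *because of this wording*, and g the excess of their mean SBP over that of the measured patients. The mean of the measured patients is below the full mean by d × g. The bias in the difference, intervention minus control, is

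−(d_I × g_I − d_C × g_C), where a negative value favours the intervention.

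5. Illustrations. The protocol supplies neither d nor g; every input here is an assumption.

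| d_I | d_C | g_I (mmHg) | g_C (mmHg) | Bias (mmHg) |
|---|---|---|---|---|
| 15% | 5% | 8 | 8 | −(1.2 − 0.4) = −0.8 |
| 20% | 10% | 5 | 5 | −(1.0 − 0.5) = −0.5 |
| 20% | 10% | 10 | 10 | −(2.0 − 1.0) = −1.0 |
| 30% | 10% | 10 | 10 | −(3.0 − 1.0) = −2.0 |
| 20% | 20% | 10 | 0 | −(2.0 − 0) = −2.0 |
| 20% | 20% | 10 | 10 | 0 |
| 20% | 10% | 5 | 10 | −(1.0 − 1.0) = 0 |
| 15% | 5% | −8 | −8 | −(−1.2 + 0.4) = +0.8 |

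6. Reading the table. Deaths, consent withdrawals and patients who cannot be traced would be missing under 7.4 as well, so they do not count towards d. For scale, the sample size allows for (458 − 382)/458 = 16.6% loss of every kind at 12 months. Shares of 20% to 30% due to this wording alone are therefore generous, and those rows are better read as upper illustrations.

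7. Precision is a lesser matter. With 80% of 229 per arm seen and SD 15 unchanged, power for 5 mmHg is 0.89; with 70% it is 0.85. The issue is selection.

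**The case against.** The strongest reply is that the protocol already has the right rule in the right place. Section 7.4 is the section on leavers, it names month 24, and it is explicit. Sections 6.8 and 8.4 are summaries, and neither says that leavers will not be invited. Their wording may simply mean patients who have not been lost or withdrawn consent, who could not be visited anyway. Section 8.5.3 adds an unrestricted 24-month entry and has patients in both groups told at month 12 that they will be called for a final visit. Section 11.2 also plans sensitivity analyses for missing data, including multiple imputation.

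Much of this stands. A reader might infer that sites would not measure any discontinued patient at month 24. That is too categorical for a site that also holds 7.4 and 8.5.3; the supported statement is that a site could omit them.

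A reader might also infer that patients who merely stop self-adjusting would be dropped. The text does not support this. Section 7.4 keeps patients who do not fully adhere, and 8.5.3 gives assessing adherence as a purpose of the month-24 visit. The heading of 7.3.2 mentions non-compliance, but its list does not name simple non-adherence as a reason for discontinuation.

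What the reply does not remove is the conflict itself. The narrow meaning of remaining in the study is nowhere stated. The limit appears in two sections, one of them the schedule, and only for month 24. Section 8.5.3 points both ways. Imputation cannot replace a measurement that could have been taken and was not sought.

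**Conclusion.** The protocol contradicts itself on who is seen at month 24, and one of the two readings is at odds with its intention-to-treat statement. The consequence is confined to the 24-month secondary comparisons of SBP, DBP, BP control and EQ-5D. The 12-month primary analysis is untouched.

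The bias cannot be sized or signed from the protocol. Under the assumptions shown, it runs from zero to about 2 mmHg in favour of the intervention when leavers have higher SBP, and it reverses if they have lower SBP. A reader might infer that it vanishes only when loss is equal across arms. That is not so: it is zero whenever the two products of share and excess match, or when leavers do not differ in BP.

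Nor does the wording show that the intention-to-treat claim fails as written, since 7.4 still states it. The point is that 6.8 and 8.4 allow conduct that would undercut it. It is worth correcting because a month-24 study measurement that is not taken cannot be recovered later, and the correction is cheap.

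**What to change.** Amend 6.8 and 8.4 to match 7.4: the 24-month visit is offered to every randomised patient who is alive and has not withdrawn consent to data collection, whether or not they still follow the assigned procedure. Change the leaver sentence in 8.5.3 in the same way, so that recording the date and reason does not end outcome follow-up for a patient who can still attend.

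The cost is wording in three places, plus a few extra invitations and visits. No sample-size figure changes. Some non-attendance will remain and falls to the missing-data analyses in 11.2. Using a BP reading from the electronic record for non-attenders is an optional sensitivity analysis that can be left to the SAP; it is not needed to resolve the contradiction.

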## **7. SELECTION AND WITHDRAWAL OF PATIENTS**

### **7.1 Inclusion criteria**

- 40 years or older
- Diagnosis of hypertension of any origin
- Systolic blood pressure (SBP) > 145 or diastolic blood pressure (DBP) > 90 mm Hg at baseline
- Voluntarily participation in the study and having signed the corresponding informed consent.

### **7.2 Exclusion criteria**

- Inability to understand and/or perform self-adjustment of the medication, including dementia or significant cognitive impairment (at the discretion of the investigator performing the recruitment).
- History of orthostatic hypotension (fall > 20 mm Hg in SBP after adopting the orthostatic position).
- SBP > 200 or DBP > 100 mm Hg on the baseline examination
- Being on treatment with more than 4 antihypertensive drugs
- Participation in another study on high blood pressure or in a clinical trial
- Presence of tremor or neurological disease that makes it difficult to perform BP self-measurement.
- Presence of arrhythmia
- Presence of terminal illness
- Chronic disability impeding to leave home
- History of acute cardiovascular event in the last 3 months
- Hypertension managed directly by specialist physicians outside the primary care setting.
- Spouse selected for the study

- Non-resident or transient patients
- Pregnancy

### **7.3 Expected criteria for withdrawal of study subjects**

#### **7.3.1 Voluntarily drop out of the study**

#### **7.3.2 For non-compliance or violation of the rules contained in the protocol**

Participating patients will have the right to withdraw from the study at any time. Additionally, the investigator may discontinue a patient from the study if she deems it necessary for any reason, including:

- Ineligibility (retrospective if not detected at enrollment)
- an adverse event leading to inability to fulfill with trial procedures
- disease progression leading to inability to fulfill with trial procedures
- withdrawal of consent
- lost to follow-up

#### **7.3.3 Women who become pregnant during the follow-up period of the study**

Since the study includes individuals over the age of 40, there is a possibility of pregnancy during the follow-up period. However, due to the naturalistic conditions of the study, it is not deemed necessary to mandate contraceptive measures for women of childbearing age. Doing so could introduce additional risks. It's important to note that the ADAMPA protocol does not involve drug administration, and any risks associated with drug treatments are unrelated to the study. These risks would arise from medications prescribed by a participant's doctor, regardless of their involvement in the study. Nonetheless, pregnancy can complicate the management of hypertension and vice versa, necessitating specific and distinct medical monitoring beyond what's outlined in the intervention protocol. Consequently, if a participant becomes pregnant during the follow-up period, they will be excluded from the assigned protocol. Instead, their care will be overseen by their doctor(s), while still maintaining their endpoint follow-up and inclusion in the intention-to-treat analysis.

### **7.4 Procedures to Follow for Patients Leaving the Study**

We will employ an intention-to-treat approach for outcome analysis. This means that all patients will be included in the analysis based on their randomized arm, even if they discontinue the trial, do not fully adhere to the intervention, or deviate from the protocol. All participants, including those who face these challenges, will be invited to attend follow-up visits at 6, 12, and 24 months. In cases of complete loss of a patient, they cannot be included in the primary analysis since the main outcome measure will not be available. If a participant abandons the study, we will document the reason in the Case Data Report (CDR) whenever possible.

## **8. MEDICATION**

### **8.1 Trial medication**

The ADAMPA study is designed to assess the effectiveness of an intervention that modifies usual clinical practice (self-monitoring and self-adjustment intervention versus usual care). It's important to note that the study does not intend to evaluate the effectiveness or safety of

medications. All medications, including antihypertensives and other therapeutic groups, will be prescribed based on the criteria of the family doctor in routine clinical practice conditions,.

### **8.2 Allowed medication**

All medications, both antihypertensives and other therapeutic groups, will be prescribed according to the family doctor's criteria in routine clinical practice conditions.

### **8.3 Acquisition, packaging and traceability of the medication used in the trial.**

As outlined in section 8.1, all medications, including antihypertensives and other therapeutic groups, will be prescribed in accordance with the criteria of the patient's family doctor, following routine clinical practice. No special conditioning or traceability will be conducted.

Patients will obtain their medications directly from pharmacies with the appropriate official medical prescription.

Nevertheless, the trial drugs' traceability is ensured through electronic prescription and dispensing systems. This technology will allow us to track both the prescriptions issued and the dispensing of medications at pharmacies throughout the trial's duration.

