**1. Summary**

Table 1. Summary of the trial characteristics

|                                       |                                                                                                                                                                                                                                                                                                                                                                                                                                                   |
|---------------------------------------|---------------------------------------------------------------------------------------------------------------------------------------------------------------------------------------------------------------------------------------------------------------------------------------------------------------------------------------------------------------------------------------------------------------------------------------------------|
| Sponsor                               | INCLIVA                                                                                                                                                                                                                                                                                                                                                                                                                                           |
| Title                                 | Impact of Self-monitoring of Blood Pressure and Self-titration of Antihypertensive Medication in the Control of Hypertension and Adherence to Treatment. A Pragmatic, Randomized, Controlled Clinical Trial (ADAMPA Study).                                                                                                                                                                                                                       |
| Protocol Code                         | ADAMPA                                                                                                                                                                                                                                                                                                                                                                                                                                            |

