| Between-group difference in Proportion of days covered with medication (PDC)                                                                                  | Secondary adherence (PDC and persistence) will be estimated using the prescription and dispensing data obtained from the Department's databases and the definitions detailed in section 6.1 will be applied.                                                                                                                                                                  |
| Difference Between Groups in Persistence                                                                                                                      |                                                                                                                                                                                                                                                                                                                                                                               |
| Difference between groups with respect to Therapeutic Inertia (IT)                                                                                            | Quotient between the number of patients whose pharmacological treatment has not been changed divided by the number of patients with SBP and/or SBP measurements taken in consultation at 6, 12, and 24 months of follow-up above the values target according to the recommendations of the European Society of Hypertension and European Society of Cardiology  . |
| Other outcome measures (tertiary endpoints):                                                                                                           |                                                                                                                                                                                                                                                                                                                                                                               |

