#### **11.2 Statistical analysis**

Analysis will be on an intention-to-treat basis for complete cases. We will use mixed models (general linear modeling –GLM) to compare SBP at 12 months between the intervention and control groups. This analysis will be presented in both crude and adjusted forms for the different covariates of interest (baseline BP, gender, GP/PCC-random effect, diabetes, etc.). A sensitivity analysis will be performed to examine the potential effect of missing data, which will include substitution by multiple imputation, replacement of data lost by the most recent data or by the mean of the series. Additionally, analyses of the main outcome measure by subgroups of age, gender, comorbidity, level of chronicity, better control at baseline, etc. will be performed.

Differences in secondary outcome measures (DBP, percentage of patients controlled, PDC, persistence and TI) will be analyzed using methods similar to those used for analysis of the main outcome measure.

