### **12.5 Protocol Compliance.**

This protocol defines the objectives and procedures of the study and the data to be collected from study participants. An investigator may not, under any circumstances, collect additional data or carry out any other procedure for any other purpose not described in the study protocol.

Investigators must exercise caution to prevent deviations from the protocol. If an investigator believes that a deviation would enhance the study's execution, it must be regarded as an amendment to the protocol. This amendment cannot be implemented until approved by the study investigators, the Clinical Research Ethics Committee (CEIm), and, when necessary, the Spanish Agency of Medicines and Medical Devices (AEMPS).

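### The protocol specifies no pre-randomisation PDC, so its adherence comparison is planned without a covariate that a look-back in the same kind of routine data could probably supply

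*Protocol*

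**What the plan says.** The title in section 1 includes "Self-titration of Antihypertensive Medication in the Control of Hypertension and Adherence to Treatment", and objective 2 in section 5.2 again names adherence. Section 6.1.2, item 5, defines the outcome as "Adherence measured by proportion of days covered (PDC) at 6 and 12 months of follow-up". Persistence (item 6) runs from the start of follow-up and is reported at the same two times. On the source, Table 4 (section 9.1) states: "Secondary adherence (PDC and persistence) will be estimated using the prescription and dispensing data obtained from the Department's databases". Neither Table 4 nor the list of data sources in section 6.6 gives an extraction window.

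Section 8.3, on traceability of the medication, says electronic prescribing and dispensing systems will make it possible to "track both the prescriptions issued and the dispensing of medications at pharmacies throughout the trial's duration".

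The baseline column of Table 2 lists antihypertensive treatments and the number of concomitant treatments, but no measure of adherence. Its footnote gives health services use a previous-year window. Section 12.2 has patients consent to access to their clinical history, including medication.

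Section 11.2 says: "Differences in secondary outcome measures (DBP, percentage of patients controlled, PDC, persistence and TI) will be analyzed using methods similar" to those for the main outcome. The adjusted SBP model there names baseline BP as a covariate, in a list left open. No earlier PDC is named.

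On entry, section 7.1 requires a diagnosis of hypertension, not current drug treatment. Section 7.2 excludes patients for "Being on treatment with more than 4 antihypertensive drugs" and sets no minimum number.

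**The concern.** Past refill behaviour usually predicts later refill behaviour, so PDC before randomisation is the natural covariate for PDC afterwards, just as baseline BP is for SBP. The protocol uses the baseline outcome for SBP and collects a baseline EQ-5D, but specifies nothing equivalent for PDC. If nobody asks for the earlier records, the adherence comparison carries residual variation that one more covariate might have removed.

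A smaller, separate matter follows from the entry criteria. A patient on no antihypertensive at randomisation has no drug to be covered or to persist with at the start of follow-up. That patient acquires a PDC only if treatment starts later, and an unmasked titration intervention can influence whether it does. With complete-case analysis (section 11.2), part of the set compared on PDC and persistence could then be formed after allocation.

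**Working it through.** **1. The plan's own figure.** Section 11.1 gives 5 mmHg, SD 15, two-sided alpha 0.05, power 90% and a total of 382. The normal approximation, 2 × (1.960 + 1.2816)² × (15/5)², gives 190 per arm after rounding up, or 380. The t-test version gives 190.1, so 191 per arm and 382 in total. Then 382 × 1.20 = 458.4, against 458 stated. The figures reproduce, but they concern SBP. The protocol gives no SD, effect or correlation for PDC.

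**2. Effect of adjustment.** Adjusting for a prior value with correlation r to the outcome multiplies the variance of the between-arm difference by (1 − r²). With m = 191 per arm, the standardised difference detectable with 90% power is (1.960 + 1.2816) × √[(2/191) × (1 − r²)]. The equivalent unadjusted total is 382/(1 − r²).

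| r (assumed) | Variance reduction | Detectable difference (SD) | Equivalent total |
|---|---|---|---|
| 0 | 0% | 0.332 | 382 |
| 0.2 | 4% | 0.325 | 398 |
| 0.3 | 9% | 0.316 | 420 |
| 0.5 | 25% | 0.287 | 509 |
| 0.7 | 49% | 0.237 | 749 |

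**3. In PDC units.** If the SD of PDC were 0.25 (an assumption), the detectable difference would be 0.332 × 0.25 = 8.3 percentage points unadjusted, 0.316 × 0.25 = 7.9 at r = 0.3, and 0.237 × 0.25 = 5.9 at r = 0.7.

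**4. If all 229 per arm contribute.** This is possible because PDC comes from databases and not from a visit. The unadjusted figure is then 3.2415 × √(2/229) = 0.303 SD. The percentage reductions do not change.

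**5. What the factor leaves out.** It applies to patients whose prior PDC is defined; the gain shrinks as the share without one grows. If other covariates already explain some of PDC, r should be read as the partial correlation, which may be lower.

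**6. Feasibility.** The source is a routine prescription and dispensing system (section 8.3, Table 4), consent reaches medication history (section 12.2), and a previous-year window is already used for another variable (Table 2 footnote). That the databases hold usable records from before randomisation is a reasonable inference; the protocol does not say so.

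**The case against.** The strongest reply is that nothing here is locked in. A reader might infer from section 8.3 that dispensing data are taken only for the trial period. The text does not support that: it describes what the systems can trace, contains no restriction, and neither section 6.6 nor Table 4 sets a start date. A reader might also infer from section 12.5, "An investigator may not, under any circumstances, collect additional data", that an analysis plan could not repair the omission. The sentence continues with a qualifier about purposes that the protocol does not describe. Adherence is a described purpose and the databases are described sources. The covariate list in section 11.2 is open, so a statistical analysis plan could add prior PDC, and an amendment is always possible. This part of the objection stands.

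It also stands that randomisation keeps the unadjusted PDC comparison unbiased among patients whose PDC is defined at entry. A chance imbalance in prior adherence is tempting to count as a further harm, but it is part of the sampling variance already in the table. Counting it again would present one loss twice. Persistence has no baseline value by construction, so the covariate argument concerns PDC.

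On untreated patients, section 10 describes the drugs as those patients already take, which suggests there are few of them. A restricted set must also be squared with the intention-to-treat commitment in section 7.4, so it should be reported as an addition.

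What the objection does not remove is that an outcome in the title has no pre-randomisation measure anywhere in the protocol. A covariate can be named later, but the data to be obtained are best stated in the protocol, which does exactly that for health services use.

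**Conclusion.** The point holds as an omission worth correcting, not as an error that undermines a result. As written, the protocol compares PDC between arms without its pre-randomisation value, although a look-back would probably supply one at little cost. The loss is of precision on a secondary outcome; the primary SBP analysis is unaffected. The gain from adjustment runs from slight (4% of variance at r = 0.2) to substantial (49% at r = 0.7). Those values of r are assumed, and usable earlier records are inferred. The lack of any entry requirement for current drug treatment is real and could let the compared set depend on allocation, but the number of patients concerned is unknown and probably small.

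**What to change.** - **Table 2 (baseline column) and Table 4:** state that prescription and dispensing data will also be extracted for the 12 months before randomisation, for every randomised patient.
- **Section 11.2:** name pre-randomisation PDC as a covariate in the PDC analysis, as baseline BP is for SBP, with an indicator for patients in whom it is undefined because they had no treatment or had only just started.
- **Section 11.2 or Table 4:** in addition to the comparison of all randomised patients, report PDC and persistence in those with at least one antihypertensive active at randomisation, a set fixed before allocation.

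The cost is an earlier start date for an extract already planned, one covariate and its indicator, and a check that the earlier records exist. No patient contact is added. Untreated patients would not contribute to the restricted comparison, which is why it should accompany the full one and not replace it.
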